### Outcome measures

All outcome measures will be recorded at baseline, immediately following the intervention period (nine weeks) and at six and 12 months post completion of the intervention (Figure 1). Baseline data collection will include age, gender, body mass index, usual ACT if previously prescribed and MMRC scale for dyspnoea [20]. The number of acute pulmonary exacerbations per year in the previous two years will also be collated. An exacerbation will be defined as an increase in clinical signs and symptoms requiring alteration of medication, including antibiotic therapy according to participant recall and medical record review.

### Primary outcome measures

The primary outcome measures are maximal exercise capacity and HRQoL. An independent assessor, blinded to group allocation will perform all outcome assessments following the intervention period (nine weeks, six and 12 months) which will be conducted over a two day period at each time point.

**a) Maximum exercise capacity **will be measured with the ISWT [29]. To allow for a learning effect, this test will be performed twice, with a 30 minute rest period in between each test. The primary outcome is the greatest distance walked. The ISWT has demonstrated a moderate to strong correlation with peak rate of oxygen uptake [30], has shown responsiveness to change following PR [12] and has been used in patients with non-CF bronchiectasis [18].

b) **HRQoL **will be measured using the CRQ (self-administered version) [31-33]. This disease-specific questionnaire has demonstrated responsiveness to change following PR [33]. The CRQ consists of 20 questions and assesses the domains of dyspnoea during activities of daily living, fatigue, emotional function and mastery, using a 7-point Likert scale and provides a total HRQoL score. A higher score indicates better HRQoL.

### Secondary outcome measures

a) **Cough specific HRQoL **will be measured using the Leicester Cough Questionnaire (LCQ). The LCQ measures the physical, psychological and social impact of chronic cough [34]. It consists of 19 items with responses based on a 7-point Likert scale and has been validated in patients with non-CF bronchiectasis [35]. A higher score indicates less impact on HRQoL.

b) **Functional exercise capacity **will be measured using the 6MWT [36]. The distance walked (6 minute walk distance, [6MWD]) has demonstrated strong correlation with peak rate of oxygen uptake and maximum work rate in patients with chronic respiratory disease [27,30]. To allow for familiarisation (or learning effect), two tests will be conducted using a standardised protocol [36] with the greatest distance recorded. The 6MWT is responsive to PR [12].

3) **Anxiety and depression **will be measured with the Hospital Anxiety and Depression Scale (HADS). This questionnaire is designed to detect and measure the severity of anxiety and depression [37]. It consists of a series of 14 statements, with responses based on a 4-point Likert scale. The HADS is self-administered and has demonstrated responsiveness to PR [38]. A higher score is indicative of greater anxiety or depression.

4) **HRQoL utility **will be measured using the Assessment of Quality of Life (AQOL) Questionnaire [39]. This measure reflects a patient's HRQoL across five dimensions: illness, independent living, social relationships, physical senses and psychological well being [39]. It is comprised of 15 questions, with the life-death utility scale score ranging from 1.00 (reflecting best possible HRQoL equivalent state) and 0.00 (worse than death equivalent state), which is then used to calculate quality adjusted life years [39]. The AQOL has been validated in different populations, but has not been previously used in individuals with bronchiectasis.

5) Symptom diary. All participants will complete a daily diary for the duration of the study, with the diaries collected at the conclusion of each assessment. Participants will record a score for quantity and colour of secretions expectorated each day. In addition, participants will also record if they have at least four of the following clinical signs and symptoms suggestive of an acute exacerbation of bronchiectasis [7] over two consecutive days:

• Increase in sputum quantity

• Change in sputum colour

• Change in sputum viscosity

• Increase in cough

• Increase in dyspnoea

• Increase in fatigue/lethargy

• Fever (self-reported)

• Episode of haemoptysis

Participants will also record occasions of unplanned review by their general practitioner or hospital admissions (duration of hospitalisation) together with the prescription of antibiotic therapy (days required) secondary to a pulmonary exacerbation of bronchiectasis in their symptom diary. These events will be cross-checked with hospital and general practitioner medical records at the conclusion of the study. Adjudication of a respiratory exacerbation will be completed by an independent investigator.

Spirometry will be performed in accordance with the American Thoracic Society guidelines [40]. The highest value for forced expiratory volume in one second (FEV_1_) and forced vital capacity (FVC) obtained from three reproducible trials will be recorded and compared to predicted normal values. This will provide a measure of the severity of airflow limitation and will be used to assess stability of lung function over the duration of the follow-up period of the study.

### Statistical analysis

Data will be entered into SPSS (version 17.0; SPSS Inc; Chi) for analysis. Descriptive statistics will be used to examine the distribution and data that are not normally distributed will be transformed or analysed using non-parametric tests. Analyses will be conducted using an intention to treat principle. Repeated measures analysis of variance with planned comparison will be used to compare all continuous variables that are normally distributed. Significant results will be analysed using post hoc tests. Categorical variables will be analysed using the chi square statistic. Relationships between outcome variables will be analysed using correlation coefficients. The alpha level for all statistical analyses will be set at 0.05.

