**Methods/Design:**

This randomised controlled trial aims to recruit 64 patients with bronchiectasis from three tertiary institutions. Participants will be randomly allocated to the intervention group (supervised, twice weekly exercise training with regular review of airway clearance therapy) or a control group (twice weekly telephone support). Measurements will be taken at baseline, immediately following the intervention and at six and 12 months following the intervention period by a blinded assessor. Exercise capacity will be measured using the incremental shuttle walk test and the six-minute walk test. Quality of life and health status will be measured using the Chronic Respiratory Questionnaire, Leicester Cough Questionnaire, Assessment of Quality of Life Questionnaire and the Hospital Anxiety and Depression Scale. The rate of hospitalisation will be captured as well as the incidence of acute pulmonary exacerbations using a daily symptom diary.

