#### Sample size

To detect a true difference in the primary outcome measures of maximal exercise capacity and HRQoL, a total of 36 subjects (18 per group) will be required. This is based on the 80% probability of detecting statistically and clinically significant differences in maximal exercise capacity (incremental shuttle walk test [ISWT]) [18] and HRQoL (Chronic Respiratory Questionnaire [CRQ] total score), according to pilot data from 33 patients with bronchiectasis who completed PR at Alfred Health. To detect a true difference for the secondary outcome measure of the incidence of acute exacerbations, a total of 64 subjects will be required. This is based on the 80% probability of detecting a true difference in the number of exacerbations between groups is 1.0 exacerbation, with a SD of 1.4 exacerbations [11].

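### Exacerbation incidence sets the sample size of 64, but none of the stated analysis methods has a term for follow-up time

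*Protocol article*

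**What the plan says.** In the Protocol article, the Background lists the incidence of acute exacerbations over 12 months as the second of two primary aims. The Sample size section calls it secondary, yet it determines the size of the trial: "To detect a true difference for the secondary outcome measure of the incidence of acute exacerbations, a total of 64 subjects will be required", against "a total of 36 subjects (18 per group) will be required" for exercise capacity and quality of life. The abstract's target matches the larger figure: "This randomised controlled trial aims to recruit 64 patients with bronchiectasis from three tertiary institutions". The calculation rests on an "80% probability of detecting a true difference in the number of exacerbations between groups is 1.0 exacerbation, with a SD of 1.4 exacerbations".

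The Statistical analysis section gives repeated measures ANOVA for normally distributed continuous variables and chi-square for categorical ones. For the rest, "data that are not normally distributed will be transformed or analysed using non-parametric tests". Analysis is by intention to treat. The section does not mention exacerbations, rates or follow-up time.

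The inputs for a rate analysis are nevertheless collected. On follow-up: "All participants will complete a daily diary for the duration of the study". On history: "The number of acute pulmonary exacerbations per year in the previous two years will also be collated". Recruitment and randomisation names the strata (sputum volume and site) and allows withdrawal at any time.

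**The concern.** A per-person exacerbation count is discrete and, with a low mean, skewed. Of the stated methods, the ones it would most naturally receive are a transformation or a rank test. Neither carries exposure time unless the count is first divided by it, and the article does not say that it will be. The Sample size section speaks of the number of exacerbations, which points to raw counts.

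On raw counts, a participant whose diary ends at month 3 and who is kept in the comparison looks like someone with few exacerbations. Loss in both arms shrinks the observed difference. Loss concentrated in one arm makes that arm look better than it is. Either would affect the outcome for which 64 − 36 = 28 of the 64 participants are recruited.

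**Working it through.** **1. The plan's own figure.** Inputs from Sample size and Statistical analysis: difference 1.0, SD 1.4, power 80%, alpha 0.05. Two-sided testing and equal arms are assumed.

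Normal approximation: n per arm = 2 × (1.960 + 0.842)² × 1.4² / 1.0² = 2 × 7.85 × 1.96 = 30.8, so 31 per arm, 62 in total. The exact t test needs 32 per arm (power 80.3%; 31 per arm gives 79.0%), which is 64. The stated figure is reproduced as a comparison of two mean counts, with no allowance for loss.

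**2. What early leaving does to raw counts.** Assume leavers exit on average halfway through the year (uniform on 0.1 to 0.9 of it). An arm with annual rate r and loss proportion d then has mean raw count r × (1 − 0.5d).

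| Assumed scenario | Control mean | PR mean | Raw difference | True difference |
|---|---|---|---|---|
| Rates 2.0 and 1.0, loss 15% in both | 2.0 × 0.925 = 1.85 | 1.0 × 0.925 = 0.925 | 0.925 | 1.0 |
| Rates 2.0 and 1.0, loss 25% control, 5% PR | 2.0 × 0.875 = 1.75 | 1.0 × 0.975 = 0.975 | 0.775 | 1.0 |
| Rate 2.5 in both, loss 5% control, 25% PR | 2.5 × 0.975 = 2.4375 | 2.5 × 0.875 = 2.1875 | 0.25 | 0 |
| Rate 2.5 in both, loss 10% control, 20% PR | 2.5 × 0.95 = 2.375 | 2.5 × 0.90 = 2.25 | 0.125 | 0 |

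For the first row, hold the plan's SD of 1.4, so the standard error is 1.4 × √(2/32) = 0.35. Normal-approximation power falls from Φ(1.0/0.35 − 1.96) = Φ(0.897) = 81.5% to Φ(0.925/0.35 − 1.96) = Φ(0.683) = 75.3%.

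**3. Type I error, by simulation.** Settings: 32 per arm, gamma-Poisson counts with over-dispersion 0.3, rate 2.5 in both arms, repeated runs of 1,500 to 3,000 trials. Monte Carlo error at 5% is √(0.05 × 0.95/1,500) = 0.6 percentage points or less.

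- Loss 5% versus 25%: spurious difference 0.24 to 0.28. Type I error is about 7–9% for the t and rank tests on raw counts, 5.2–5.7% for a rate model with offset, and 5.5% for a rank test on each person's annualised rate.
- Loss 10% versus 20%: t 6.2%, rank on raw counts 5.6%, rate model 6.0%. No practical inflation.
- Loss 10% in both arms: all about 5%.

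The result depends on the count distribution. With rate 2 in both arms and loss 10% versus 30%, Poisson counts give 8.7% (t) and 9.1% (rank). Counts with variance 4 give 6.4% and 7.3%.

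**4. Power, by simulation (rates 2.0 and 1.0, over-dispersion 0.3).**

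| Loss | Rank test, raw counts | Rate model with offset |
|---|---|---|
| None | 70–72% | 77% |
| 15% in both | 66–67% | 73–75% |
| 25% control, 5% PR | 47–48% | 73–75% |

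With no loss the gap is already 5 to 7 points. At equal 15% loss it is 6 to 9. Most of the gap at equal loss therefore comes from using ranks and not from ignoring time. This scenario also has a larger SD than planned: variances 2 + 0.3 × 4 = 3.2 and 1 + 0.3 × 1 = 1.3, average 2.25, SD 1.5 against 1.4.

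**The case against.** The best defence is that this is a condensed article whose Statistical analysis section does not name exacerbations and does not claim to list every method. A model for a count outcome could sit in an analysis plan that is not shown. The text also permits a rank test on annualised rates, which in the scenario above returns type I error to about 5%. This stands in part: the article leaves the choice open and does not commit to a wrong analysis. But where it does describe the outcome numerically, in Sample size, it uses a number of exacerbations, and nothing directs the analyst to divide by follow-up time.

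A reader might infer that early leavers must be either dropped or counted as low-exacerbation cases. The documents do not support that. Annualising is allowed, and Secondary outcome measures plans a hospital and general practitioner record check with independent adjudication. The check is described for events entered in the diary, however, so capture after a diary stops is not explicit.

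A reader might also infer that loss will differ by arm, because one arm attends 16 supervised sessions and the other receives telephone calls. That is plausible but undocumented. No loss rate is given, both arms keep the same symptom diary and attend the same assessments, and the twice-weekly calls are meant to balance clinician contact.

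Finally, leaving the exacerbation history out of the analysis is not an error. Adjusting for it is an efficiency gain, put at about 2 to 6 points of power in simulation.

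**Conclusion.** The point holds in a limited form. The outcome that sets the trial's size is framed as a raw count, the aim asks for incidence, withdrawal is allowed at any time, and no stated method accounts for time at risk.

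The size rests on assumed rates and loss. Equal loss of 15% reduces a true difference of 1.0 to about 0.9 and costs roughly 6 points of power (81.5% to 75.3%). Loss of 5% versus 25% creates a spurious difference of about 0.25, a quarter of the target, with type I error of about 7–9%. If the heavier loss is in the control arm, a real benefit is partly hidden instead.

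Three stronger readings are not supported: that false positives are inflated in general (little or nothing is seen at 10% versus 20% or equal loss), that the rank test's lower power is mainly a follow-up problem, and that the figure of 64 is wrong on its own inputs. Exacerbations are labelled secondary and the primary outcomes are unaffected. This should be fixed, but it does not undermine the trial.

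**What to change.** State that adjudicated exacerbations, counted from randomisation, will be analysed by negative binomial regression (or quasi-Poisson), with log follow-up time as offset and with site, sputum stratum and prior exacerbation rate as covariates. Report the rate ratio with a 95% confidence interval. Define when time at risk ends for someone who stops the diary, and whether the record check extends it.

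The cost is analysis wording: the diary, adjudication, strata and history are already planned. The downsides are small. A model-based rate ratio replaces a simple difference in means, and 64 patients give few events per stratum, so the covariate set may need to be kept lean. The offset corrects for unequal follow-up time; it does not correct for participants leaving because of their exacerbations.

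### If a primary outcome looks non-normal, the plan leaves open which effect measure it reports: the switch depends on the observed data and the two fallbacks are unordered

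*Protocol article*

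**What the plan says.** The protocol article's Statistical analysis section gives one rule for every continuous outcome:

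- The screen and the fallback: distributions are first inspected descriptively, and "data that are not normally distributed will be transformed or analysed using non-parametric tests".
- The default: "Repeated measures analysis of variance with planned comparison will be used to compare all continuous variables that are normally distributed".
- The significance level: "The alpha level for all statistical analyses will be set at 0.05".

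The section on primary outcomes states that "The primary outcome measures are maximal exercise capacity and HRQoL". For the ISWT, "The primary outcome is the greatest distance walked". The CRQ is described as "using a 7-point Likert scale and provides a total HRQoL score". Neither outcome is given an analysis rule of its own.

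The Sample size section plans on an "80% probability of detecting statistically and clinically significant differences in maximal exercise capacity" and on the CRQ total score. It prints neither the difference nor the SD for either one.

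**The concern.** The rule makes the method for both primary outcomes depend on how the collected data look. If they look normal, the result is a difference in mean metres or mean CRQ points. If not, the analyst may transform or may use a rank test, and nothing says which comes first.

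These routes do not estimate the same thing. An analysis of logged distance gives a ratio of geometric means. A rank test gives a shift in ranks or a probability of superiority. The planning statement speaks of clinically significant differences in ISWT and CRQ total score, which a reader would judge in metres and points. The headline result might not be on that scale, and ISWT and CRQ could end up on different scales from each other.

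There is also a question of error rate. An unordered choice made with outcome data in hand gives room to prefer the fallback with the smaller p-value.

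**Working it through.** **1. The plan's own figures.** The only sample size with full inputs is the 64 for exacerbations (difference 1.0, SD 1.4, 80% power, alpha 0.05, taken as two-sided). Per group, n = 2 × (1.960 + 0.842)² × 1.4² / 1.0² = 30.8, so 31. With the t distribution it is 32 (power 0.803, against 0.790 at 31), giving 64, so the stated figure reproduces. The 36 for the primaries cannot be checked without a difference and SD. By the normal approximation, 18 per group implies a standardised difference of √(2/18) × 2.802 = 0.93. The point below does not depend on either figure, but they set the group sizes used: 18 and 32.

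**2. What each branch estimates.**

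| Branch | Effect measure | In metres or points? |
|---|---|---|
| Looks normal: repeated measures ANOVA | Difference in means | Yes |
| Not normal, log transformation | Ratio of geometric means | No; a ratio r means a gain of (r − 1) × the reference distance, which differs between patients |
| Not normal, rank test | Rank shift or probability of superiority | No |

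This step needs no distributional assumption beyond a primary outcome being judged non-normal.

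**3. Type I error.** Null simulation, 60,000 runs per setting, two groups at one time point. *Assumptions:* log-normal outcome with log-SD 0.35 or 0.6; screen = skewness test at 0.05 on pooled within-group residuals; two-sided tests at 0.05. The rank-sum test used z = (|R − n(2n+1)/2| − 0.5) / √(n²(2n+1)/12). The simulation standard error is √(0.05 × 0.95 / 60,000) = 0.09 percentage points. Entries are percentages.

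| log-SD | n per group | Flagged | t | log t | Rank | Screen, then rank | Screen, then log t | Screen, then smaller p of the two | Smallest p of all three |
|---|---|---|---|---|---|---|---|---|---|
| 0.35 | 18 | 51.1 | 4.93 | 5.00 | 4.67 | 5.30 | 5.37 | 5.86 | 6.38 |
| 0.35 | 32 | 79.0 | 4.77 | 4.85 | 4.69 | 5.03 | 5.12 | 5.83 | 6.46 |
| 0.6 | 18 | 84.9 | 4.61 | 5.05 | 4.81 | 5.17 | 5.39 | 6.15 | 6.89 |
| 0.6 | 32 | 98.5 | 4.62 | 4.89 | 4.79 | 4.83 | 4.96 | 5.89 | 6.99 |

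- Any single pre-named test holds about 5%, including the untransformed t test on skewed data.
- Screening followed by one fixed fallback gives 4.8% to 5.4%.
- Screening followed by the more favourable fallback gives 5.8% to 6.2%.
- Picking freely among all three gives 6.4% to 7.0%. This ignores the plan's own screen.

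Other simulations used a Shapiro-Wilk screen and stronger skew (log-SD 0.5 to 0.8, 32 per group, 8,000 runs), with a square-root transformation as a further option. They gave 6.3% to 6.7% for the most favourable fallback and 6.9% to 7.5% for free choice.

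**4. Stability of the branch.** With moderate skew and 18 per group the screen fires in 51% of trials, so chance largely decides the effect measure. Under normal data, Shapiro-Wilk in each group at 0.05 should fire in 1 − 0.95² = 9.75% of trials; simulation gave 9.4% at 18 and 10.2% at 32 per group.

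**The case against.** **A default is named.** A reader might infer that the primary analysis is wholly unspecified. The text does not support that: repeated measures ANOVA with planned comparison is stated, and only the switch and the fallback are open. The article gives no distribution for ISWT or CRQ total, so the switch may never be used. This stands, and it limits the point to the case where a primary outcome looks non-normal.

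**Detail belongs in the analysis plan.** Which transformation, which rank test, which criterion, and whether residuals or raw values are inspected are commonly settled in an SAP, which is not shown. The article's reference to data may be shorthand for residuals, so no weight is put on that. But the point is not a missing detail. The article states a data-dependent rule. An SAP that follows it keeps the switch, and one that fixes a single model regardless of distribution departs from it.

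**The error rate.** A reader might infer that the 0.05 level is not held. The simulations do not show that. Followed without regard to results, the rule stays near 5%. The excess needs selective choice, which the plan does not describe.

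**Power.** A reader might also infer a large power loss by setting an unadjusted rank test on follow-up values (about 47% at a 0.5 SD effect, 32 per group) against a baseline-adjusted model (68% or 89%, at assumed baseline correlations of 0.6 or 0.8). That gap is almost all baseline adjustment. By the normal approximation, the unadjusted comparison has 0.5 × √(32/2) = 2.0 standard errors, hence power of about 51%. Adjustment raises this to 2.0/√(1 − 0.6²) = 2.5 or 2.0/√(1 − 0.8²) = 3.3. An unadjusted rank test gives about 48%, so the test itself costs about 3 points. Under strong skew the rank test did as well or better. Power is not evidence against the selection rule.

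**Conclusion.** The point holds in a limited form. For both primary outcomes the plan makes the method depend on the observed distribution and leaves two fallbacks unordered. If either outcome is judged non-normal, its effect measure is not fixed in advance and may not be in the units in which clinical significance is judged. That conclusion rests on the text alone and holds even if nobody looks at a p-value before choosing.

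The type I error consequence is secondary: near 5% with one fallback applied without regard to results, about 5.5% to 6.5% if the fallback is chosen with results in view, and about 7% or slightly more at worst. These figures are per outcome and per time point. They rest on assumed log-normal data, an assumed screen, and a two-group test standing in for the repeated measures analysis. The article neither supports nor excludes that degree of skew for a walking distance or a 20-item total score.

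This is worth correcting before the data are unblinded. It does not undermine the design.

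**What to change.** Replace the distribution-dependent rule for the two primary outcomes with one pre-named analysis:

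- Analyse ISWT distance and CRQ total score on their original scale by one model whatever the distribution. An example is a linear mixed model with arm, visit, arm-by-visit, baseline value and the two stratification factors (sputum quantity and site).
- Report the arm difference in metres or points with a 95% CI as the primary result.
- Check the residuals, and give a named rank-based or transformed analysis as a sensitivity analysis that does not replace the primary result.

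Merely ordering the fallbacks before unblinding would remove the room for selective choice, but the effect measure would still depend on the data.

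The cost is a few lines of analysis text and no new data, since baseline values and stratification factors are already collected. The downside is some loss of efficiency if an outcome proves strongly skewed, which the sensitivity analysis would show. Any precision gained from baseline adjustment is a separate benefit whose size depends on correlations the article does not give.

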**Figure 1 F1:**
[figure not shown]
**Flow of patients through the study**.

Participants will be screened from the Lung Institute of Western Australia (LIWA) database of individuals with bronchiectasis or during outpatient clinic visits to Physiotherapy or Respiratory Medicine at Alfred Health, Austin Health and Sir Charles Gairdner Hospital, by the study investigators. If eligible, the study investigators will approach the participant to explain the study and gain written, informed consent. It will be explained that they may withdraw from the study at any time. Within strata, participants will be randomly assigned to receive either standard care alone or PR. The strata are sputum quantity (small volume: up to one tablespoon per day, large volume: > one tablespoon per day) and the site of randomisation. The randomisation will be completed by the creation of a random numbers table and individual group assignment will be kept in sealed opaque envelopes. Following baseline assessments, a physiotherapist will collect the appropriate envelope after confirming sputum quantity. A computer-generated randomised order for performing the field walking tests for each participant will be determined before baseline measures and adhered to throughout the study.

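### Run as written, repeated measures ANOVA drops anyone who misses one of the four visits, which weakens the intention-to-treat claim and can bias the primary comparisons

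*Protocol article*

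**What the plan says.** The Statistical analysis section of the protocol article sets the principle: "Analyses will be conducted using an intention to treat principle". Its next sentence sets the method: "Repeated measures analysis of variance with planned comparison will be used to compare all continuous variables that are normally distributed". Variables that are not normally distributed are to be transformed or analysed non-parametrically. The section does not say what happens to a participant with a missed visit.

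Under Outcome measures, assessments take place "at baseline, immediately following the intervention period (nine weeks) and at six and 12 months post completion of the intervention", so the within-subject factor has four levels over roughly 14 months. Under Primary outcome measures, "The primary outcome measures are maximal exercise capacity and HRQoL". These are ISWT distance and the CRQ, both continuous, so the ANOVA sentence covers them whenever they are normal or can be made so by transformation.

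Loss is foreseen. On consent, the Recruitment and randomisation section says: "It will be explained that they may withdraw from the study at any time". The Background hypothesises that the gains in exercise capacity and HRQoL last for up to six months. The Sample size section requires 36 participants (18 per group) for the primary outcomes and 64 for exacerbations, and 64 is the recruitment target.

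**The concern.** Classical repeated measures ANOVA works on participants observed at every level of the within-subject factor. Someone seen at baseline, nine weeks and six months but not at 12 months has an incomplete row and is removed from the whole analysis. Data already collected for the visits that matter most to the hypothesis are discarded because a later visit was missed. The set analysed is then those with all four assessments, not all those randomised who have data.

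Missed visits are plausible here. Participants must have had at least two exacerbations a year for two years, and each follow-up assessment is spread over two days. If the reasons for absence relate to outcome, and do so differently in the two arms, the comparison among those with full data no longer estimates the effect of being allocated to rehabilitation. In the rehabilitation arm, absence may also reflect disappointment with the programme, a reason that does not exist in the same form in the telephone-support arm.

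**Working it through.** **1. The plan's own sample size.** Inputs from Sample size: difference 1.0 exacerbation, SD 1.4, power 80%. Alpha is 0.05 (Statistical analysis) and is taken as two-sided. The standardised difference is 1.0/1.4 = 0.714. A two-sample t-test needs 31.76, so 32 per arm and 64 in total, with power 80.3%. The stated 64 reproduces and contains no allowance for loss.

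For the primary outcomes no difference or SD is printed, so the 36 cannot be reproduced. It can be inverted: 18 per group at 80% power and two-sided 0.05 implies a standardised difference of d = 0.96.

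**2. How many rows would be complete.** No dropout rate is given, so this is an assumption. If each of the three follow-up visits is missed independently with probability q, the complete share is (1 − q)³.

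| q | (1 − q)³ | complete rows of 64 | power at d = 0.96 |
|---|---|---|---|
| 5% | 0.857 | 54.9 | 93.8% |
| 10% | 0.729 | 46.7 | 89.5% |
| 15% | 0.614 | 39.3 | 83.5% |
| 20% | 0.512 | 32.8 | 75.9% |

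Complete rows fall to the required 36 when (1 − q)³ = 36/64 = 0.5625, that is q = 1 − 0.5625^(1/3) = 17%. If loss is permanent dropout instead, 10, 20 or 30% lost by 12 months leaves 57.6, 51.2 or 44.8 of 64, with power of 95, 92 or 88% at the same d.

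So at q of 5 to 10%, between 64 − 55 = 9 and 64 − 47 = 17 randomised participants would drop out of every comparison, yet power for the primary outcomes stays above the planned 80%.

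**3. What deletion can do to the nine-week contrast.** A simulation with 400,000 per arm illustrates the mechanism. All of its settings are assumed:

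- correlation of 0.7 between any two visits;
- a true nine-week effect of 0.50 SD;
- everyone seen at nine weeks;
- in the rehabilitation arm, poorer nine-week change makes later loss more likely (logistic, slope 1.5 per SD of change);
- in the control arm, loss at random at the same overall rate.

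| later loss | nine-week effect, all participants | nine-week effect, complete rows only |
|---|---|---|
| 10% | 0.50 SD | 0.59 SD |
| 20% | 0.50 SD | 0.68 SD |
| 30% | 0.50 SD | 0.75 SD |

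Every nine-week value was observed. The distortion arises only because participants lost later are deleted from the nine-week comparison. With a different loss mechanism the bias could be smaller, absent or in the other direction.

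**The case against.** The strongest reply is that the article names a principle and a test, not listwise deletion. Intention to treat can mean analysing people in the arm to which they were allocated, whether or not they attended 12 of 16 sessions, and nothing in Statistical analysis breaks that. ANOVA after imputation would fit both sentences, as would a loose use of the term for a mixed model. A full analysis plan, not shown, may settle it. This stands as a condition: the consequence follows only if values are not imputed first and the term carries its usual meaning. A reader might infer that the two sentences flatly contradict each other, but the documents do not support that. It does not remove the point, because the article fixes a particular method, and that method in its usual form deletes incomplete rows. The non-parametric alternative is no clear escape, since a test such as Friedman's also needs complete rows.

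A reader might also infer a serious loss of power. Applying d = 0.714 to 47 to 55 complete rows gives about 67 to 74%. That effect size belongs to the exacerbation calculation, which Sample size treats as secondary. Exacerbation incidence is a count from a daily diary, with no evident four-visit row to delete. The figure therefore describes neither primary outcome and should not be used.

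Finally, bias is not a certainty. A contrast between arms is distorted when missingness relates to outcome differently by arm, and the simulation had to assume that. The documents give neither the amount of loss nor its pattern. That too stands.

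**Conclusion.** The point holds in conditional form. With no imputation stated, the named method omits every participant who misses any of the four visits, including from the nine-week and six-month comparisons. Not all randomised participants with data would be analysed, which sits badly with the intention-to-treat sentence just before it. Here, having complete data means having all assessments; it does not mean having completed the exercise programme, and the article does not say that non-attenders are excluded.

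The cost is possible bias of unknown size and direction, discarded data and a weaker intention-to-treat claim. Power is largely protected because 64 are recruited against 36 required: about 90 to 94% at d = 0.96 with an assumed 5 to 10% missed independently at each follow-up visit. These power figures rest on the d implied by 18 per group, a two-sided 0.05 test, equal arms and a simple two-sample comparison.

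**What to change.** In Statistical analysis, replace repeated measures ANOVA for the continuous outcomes with a likelihood-based linear mixed model for repeated measures. The outcomes are the values at nine weeks, six months and 12 months. The terms are arm, visit, arm-by-visit, the baseline value, and the two stratification factors named under Recruitment and randomisation (site and sputum volume). Include every randomised participant with at least one follow-up value in the arm allocated, and report the arm difference with a 95% confidence interval at each visit.

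If the team prefers to keep ANOVA, the smallest change that reconciles the two sentences is to state the imputation method to be applied first.

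The cost is wording and modest analysis work; visits, recruitment and treatment do not change. The small downside is that the mixed model relies on data being missing at random. One sensitivity analysis that departs from that assumption can probe it. Participants with no follow-up value at all would still contribute nothing to the model, and their number should be reported by arm.
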